## Abstract

**Background::**

Presentation of musculoskeletal symptoms, such as pain, discomfort, or disability, caused by a traffic accident (TA) is a common occurrence. However, studies on treatment and management of sudden low back pain (LBP) caused by a TA are very scarce, while studies on the effectiveness of motion style acupuncture therapy (MSAT) used on such patients are also rare. Accordingly, a randomized controlled trial (RCT) is planned to assess the effectiveness and safety of MSAT using traction (T-MSAT) for the treatment of pain and functional problems in patients with acute LBP caused by a TA.

**Methods::**

This study will be conducted at Jaseng Hospital of Korean Medicine in South Korea, using a two-armed, parallel, assessor-blinded RCT design. The study population will consist of 100 participants who will be randomly assigned in a 1:1 ratio to either the T-MSAT+integrative Korean medicine therapy (IKMT) group or IKMT control group. The treatment will be applied continuously for 3 days after admission. The primary outcome will be the difference between the numeric rating scale (NRS) scores at admission and immediately after treatment on the fourth day of admission. Secondary outcomes will include visual analogue scale (VAS) for LBP and radiating leg pain; NRS for radiating leg pain; lumbar active range of motion; Oswestry Disability Index (ODI); Patient Global Impression of Change (PGIC); the Post-traumatic Stress Disorder Checklist for DSM-5 (PCL-5-K); and 12-item short-form health survey (SF-12).

**Discussion::**

This study is a RCT to assess the effectiveness and safety of T-MSAT for acute LBP caused by a TA. The findings could be used by healthcare-related policy makers and clinicians in primary care institutions, which are frequently visited by patients suffering from LBP caused by a TA.

## Introduction

1

Low back pain (LBP) is a common disorder, with over 80% of the world population experiencing at least 1 episode in their lifetime, and frequent recurrences may affect the quality of life of an individual.^[1]^ According to the Global Burden of Disease Study, the population affected by LBP increased significantly over a 30-year period between 1990 and 2017, as did the number of years lost due to disability (YLD) associated with LBP; thus, LBP can be viewed as a disorder that has a detrimental effect on quality of life (QoL).^[2]^ Persistent LBP restricts normal activities and causes occupational disability that not only affects the QoL of individuals, but also causes social and economic losses.^[3,4]^

The definition of acute LBP varies between studies, but typically refers to LBP that has occurred within 4 to 6 weeks, while LBP that persists for 12 weeks or more is categorized as chronic LBP.^[5]^ After the onset of acute LBP, recurrence of pain is found in more than half of cases and the overall recurrence rate is up to 75%.^[6]^ The global prevalence of LBP is 18.3% at any given time, while the 1-month and 1-year prevalence is 30.8% and 38%, respectively.^[7]^ Therefore, it is important to treat acute LBP in a timely manner to prevent progression to the chronic phase. Therapies used for LBP in the acute phase include bed rest; drug therapy, such as analgesics and herbal medicine; exercise therapy; acupuncture; electromyographic biofeedback; epidural steroid injections; and spinal manipulative therapy.^[5,6]^

With improved road conditions and advances in various modes of transportation, the number of cars owned by Koreans has increased exponentially from 530,000 in 1980 to 23.67 million in 2019. Accordingly, the number of car traffic accidents (TAs) reached 1,292,864 cases in 2019, representing an average annual increase of 3.1% since 2010, while the total number of injuries has also increased by an average of 3.3% each year.^[8]^

After a TA, various musculoskeletal injuries, internal bruises, and psychological trauma may result,^[9,10]^ while common symptoms after a TA often include neck pain or LBP.^[11,12]^ One study reported that approximately 37% of patients complained of severe LBP only 6 weeks after a TA and 23% of cases involved both neck and LBP.^[9]^ Another cohort study reported that 60.4% of patients who were treated within 30 days of an accident complained of LBP.^[13]^ Acute LBP caused by a TA could easily linger, with 1 study reporting 31% of cases presented with LBP up to 1 year after the initial injury.^[14]^ In particular, people with a history of LBP have a high risk of developing chronic LBP after an accident,^[12,15]^ and should, therefore, be managed with close attention.

Motion style acupuncture therapy (MSAT) refers to a therapeutic method in which the patient makes active or passive movements with acupuncture needles inserted in the body.^[16]^ MSAT is not only used in Korea, but also in China, for pain reduction and functional improvement for various musculoskeletal disorders, with greater efficacy than traditional acupuncture therapy.^[16–19]^ MSAT using traction (T-MSAT) utilizes a traction device to pull the body of the patient, after which, the practitioner instructs the patient to walk with the acupuncture needles already inserted to resolve lumbar musculoskeletal disorders.

Guidelines for acute LBP recommend the patient stays active and avoids bed rest, while some studies have mentioned walking or traction therapy.^[20,21]^ A study comparing T-MSAT to analgesic injection in patients with serious lumbar dysfunction reported that the pain reduction effect of MSAT was at least 5 times greater than that of the analgesic injection;^[16]^ however, studies on T-MSAT are scarce, and the evidence for the effectiveness and safety of T-MSAT is lacking.

Accordingly, this randomized controlled trial (RCT) plans to assess the effectiveness and safety of T-MSAT in patients with acute LBP caused by a TA.

## Method

2

This study is described in accordance with the SPIRIT 2013 Statement.

### Objectives

2.1

We plan to conduct an RCT to investigate the effectiveness and safety of T-MSAT in the improvement of conditions of patients with LBP and lumbar dysfunction.

We will investigate LBP score, lumbar dysfunction index, QoL, post-traumatic stress, and any adverse reactions, to assess the comparative effectiveness and safety between T-MSAT combination therapy and inpatient integrative Korean medicine therapy (IKMT).

### Study design and setting

2.2

The study trial design is detailed in Figure 1. This study will be based on a two-arm parallel, single blinded (outcome assessor blinded) RCT protocol. The clinical trial will be conducted in Jaseng Hospital of Korean Medicine (South Korea). Among people injured following TAs occurring within 1 week, 100 patients will be recruited in accordance with the inclusion and exclusion criteria (Table 1). The trial protocol was approved prior to participant recruitment by the Institutional Review Board (IRB) of the institution conducting the trial (IRB 2020-08-011). This study is registered on Clinicaltrials.gov (Clinical trials ID: NCT04554446). And the progress of the trial will be continuously updated.

**Figure 1 F1:**
[figure not shown]
Trial flow. D/C = discharge, F/U = follow-up, LBP = lower back pain, NRS = numeric rating scale, ODI = Oswestry Disability Index, PCL-5-K = Post-traumatic Stress Disorder Checklist for DSM-5, PGIC = Patient Global Impression of Change, ROM = range of motion, SF-12 = 12-item short-form health survey, VAS = visual analogue scale.

**Table 1 T1:** Inclusion and exclusion criteria.

Inclusion criteria	Exclusion criteria
1. Patients aged 19–70 years	1. Patients who have been diagnosed with a specific disease that may cause acute LBP (tumor metastasis to the spine, acute fracture, dislocation of the spinal column, etc.)
2. Patients with NRS for LBP ≥5	2. Patients with progressive neurological deficit or LBP accompanied by serious neurological symptoms
3. Patients who require inpatient treatment for acute LBP caused by a TA that occurred within one week	3. Cases in which the cause of pain is attributable to a soft tissue disorder, not the spine (tumor, fibromyalgia, rheumatoid arthritis, gout, etc.)
4. Patients who voluntarily agree to participate in the study and submit an informed consent form	4. Cases involving other chronic diseases that may interfere with the interpretation of therapeutic effects or outcomes (stroke, myocardial infarction, kidney disease, diabetic neuropathy, dementia, epilepsy, etc.)
	5. Ambulatory difficulty due to lower extremity dysfunction unrelated to LBP
	6. Patients currently taking steroids, immunosuppressants, mental illness drugs, or other drugs that may affect the study outcome
	7. Patients who are pregnant, planning to become pregnant, or breastfeeding
	8. Patients who underwent any surgery or procedure on the lumbar region within the past three weeks
	9. Patients with severe mental disorder
	10. Patients who have completed their participation in another clinical trial within the past one month or are planning to participate in another clinical trial within 12 weeks of being selected for this clinical trial or during the F/U period of this clinical trial
	11. Patients with difficulty completing the informed consent form
	12. Others who the researcher determines to be unfit to participate in the clinical trial

Among patients hospitalized at Jaseng Hospital of Korean Medicine for injuries caused by a TA, participants for this study will be recruited by posters inside the hospital, the hospital website, and physician recommendations. The recruitment will begin in September 2020.Candidates will listen to an explanation about the study given by the researcher on the first day of hospitalization (D1) and only those who voluntarily agree to participate in the study will fill out an informed consent form. Subsequently, the screening researcher will apply the inclusion and exclusion criteria (Table 1), and only 100 patients who satisfy the criteria will be selected and enrolled in the study.

The participants will be required to complete 6 visits (Vs), including the first day of hospitalization. All surveys will be conducted by face-to-face interview method, except the follow-up (F/U) survey (12 weeks after registration), which may be replaced by a telephone interview. On the second day of hospitalization (D2), the participants will be randomly assigned in a 1:1 ratio to the T-MSAT+IKMT group (N = 50) and IKMT group (N = 50) to undergo treatment. All management of participants and treatment processes will follow the trial protocol.

### Randomization and allocation concealment

2.3

A statistics expert, not directly involved with the study, will use SAS Version 9.4 (SAS institute. Inc, Cary, NC) for block randomization to assign an equal number of participants to each group (50 per group). Randomization will be applied all 100 patients according to single-center patient recruitment/registration; the results will be sealed in envelopes and relayed to the center to be kept in a double-lock locker. The envelope will be opened in the presence of the selected participant before the treatment, after which the random allocation number will be recorded in the electronic chart. Once the allocation is made no further changes will be possible.

### Blinding

2.4

Because the design used in this study does not allow blinding of both the patients and therapist to the respective group allocation, only the assessor will be blinded (single blind design). The assessor will not take part in the intervention. A researcher who will remain blinded to the group allocation will perform the assessment in a separate area prior to the intervention.

### Interventions

2.5

The study population (n = 100) will be randomly allocated to 2 groups: IKMT only group (n = 50) and T-MSAT combined (T-MSAT+IKMT) therapy group (n = 50). The IKMT group will receive acupuncture, Chuna therapy, pharmacopuncture therapy, and herbal medicine; while the T-MSAT+IKMT group will also receive T-MSAT. The interventions in this study will be conducted by a physician who has been trained in advance in accordance with the reported protocol.

#### Experimental group: T-MSAT+IKMT

2.5.1

The T-MSAT+IKMT group will take part in 3 sessions (once a day between D2 and D4). During the 3 sessions of T-MSAT, the group will also take part in IKMT sessions. A doctor of Korean medicine with over 18 months of clinical experience will use a T-MSAT device to apply traction to the patients body, after which needles will be inserted into 6 to 12 acupoints (including BL23, BL54, SP6, GB39, and Ashi acupoints), and the doctor will instruct the patient to walk. The duration of the intervention may be adjusted depending on pain or discomfort felt by the patient.

#### Control group: IKMT group

2.5.2

The treatment for the control group will consist of only IKMT, and will include acupuncture, pharmacopuncture therapy, Chuna therapy, and herbal medicine. The treatment will be applied during hospitalization by an experienced doctor of Korean medicine.

#### Co-interventions

2.5.3

When deemed necessary due to severe pain experienced during participation in the study (including treatment and F/U periods), use of other treatments that may affect the assessment of LBP will not be restricted. The participant will immediately notify the principal investigator who shall monitor and record adverse reactions and medication used.

### Participants schedule

2.6

This study will be conducted as per the schedule provided in Table 2.

**Table 2 T2:** Schedule of treatment.

	Study period					
	Screening	Active treatment				F/U
Time point	Day 1 of hospitalization	Day 2 (visit 1)	Day 3 (visit 2)	Day 4 (visit 3)	Discharge (visit 4)	12 weeks after registration (visit 5)
Enrollment						
Eligibility screening	○					
Written Informed consent	○					
Sociodemographic characteristics	○					
Information about TA^a^	○					
Medical history (post LBP, and other)	○					
Physical examination	○					
Randomized allocation		○				
Credibility and Expectancy Questionnaire		○				
Intervention						
T-MSAT+IKMT	Δ (only IKMT)	○	○	○	Δ (only IKMT)	
IKMT	○	○	○	○	○	
Assessment						
Check symptoms and Medication change		○	○	○	○	○
NRS of LBP	○	○^∗^	○	○^∗^	○	○
VAS of LBP		○^†^	○	○^†^	○	
ROM of lumbar spine		○^‡^	○	○^‡^	○	
NRS of leg pain		○^§^	○	○^§^	○	○
VAS of leg pain		○^||^	○	○^||^	○	
ODI		○		○^¶^	○	○
SF-12		○		○^¶^	○	○
PGIC				○^¶^	○	○
PCL-5-K		○		○^¶^	○	○
Diagnostic imaging^b^						○
Details of F/U^c^						○
Adverse events		○	○	○	○	○

### Outcome measures

2.7

The outcomes will be measured at each time point during 12 weeks of the study period, and the primary endpoint is D4 (V3) when the treatment is completed.

#### Primary outcome

2.7.1

The primary outcome will be the difference between numeric rating scale (NRS) for LBP at admission and at completion of treatment on D4. NRS is a pain scale used to express the subjective pain felt by the patient as an objective numerical value. The patient is instructed to select a number between 0 (no pain) and 10 (worst pain imaginable) that best describes their current pain level.^[22,23]^

#### Secondary outcomes

2.7.2

Secondary outcomes will be assessed by NRS for radiating leg pain; visual analogue scale (VAS) for lumbar and radiating leg pain; lumbar active range of motion (aROM); Oswestry Disability Index (ODI); 12-item short-form health survey (SF-12); Post-traumatic Stress Disorder Checklist for DSM-5 (PCL-5-K); and Patient Global Impression of Change (PGIC). In addition, F/U investigation will be conducted at 12 weeks after study registration to assess: NRS for leg and LBP; NRS; ODI; SF-12; PCL-5-K; and PGIC, and radiological findings from lumbar imaging performed after TA (L-spine X-ray, L-spine MRI, and L-spine CT) will be recorded, while accident settlement, completion of treatment, and return to work will also be investigated.

VAS for LBP and radiating leg pain: VAS is an assessment tool for recording pain felt by a patient using a line that is 100 mm long, with one end indicating no pain and the other end indicating worst pain imaginable.^[22,24]^ To identify the level of LBP and radiating leg pain felt, the patient will be instructed to indicate a point on the line that best describes his or her level of pain.

NRS of leg pain: The patient will be instructed to select a numerical value between 0 (no pain) and 10 (worst pain imaginable) that best describes the subjective radiating leg pain he or she is feeling.

Lumbar aROM by physical examination: The lumbar aROM that allows the patient to move without pain will be measured. The lumbar aROM in 6 directions (flexion, extension, right lateral flexion, left lateral flexion, right rotation, and left rotation) will be measured.

ODI: The low back functional disability of patient will be assessed using the ODI questionnaire.^[25]^ ODI is a 10-item tool developed for assessing level of low back functional disability, with each item divided into 6 stages and assigned 0 to 5 points. Higher total scores indicate more severe disability and this study will use the official Korean version of the ODI questionnaire.^[26]^

Korean version of health-related QoL (HRQoL) assessment scale (SF-12 v2): SF-12 v2 is a questionnaire used to assess HRQoL, comprising 12 items in 8 categories (physical function, role-physical, bodily pain, general health, vitality, social function, role-emotional, and mental health). This tool will used in this study to assess the level of functional health and life, with higher scores indicating better HRQoL. For the Korean version of SF-12, Kim et al tested the reliability and validity to measure HRQoL in 1000 Koreans.^[27]^

PCL-5-K: Post-traumatic stress disorder (PTSD) checklist (PCL) is one of the most widely used self-reporting scale for assessing PTSD. This tool will be used in this study to measure the degree of stress in the patient caused by a traumatic factor in the form of a TA. The study will use the Korean version of the checklist adapted into Korean by Kim et al^[28]^ and subsequently tested for reliability and validity.

Global assessment scale (PGIC): PGIC is a method used to subjectively assess the degree of improvement in a patients condition, divided into 7 steps^[29,30]^: 1 = very much improved; 2 = much improved; 3 = minimally improved; 4 = no change; 5 = minimally worse; 6 = much worse; and 7 = very much worse. In this study, PGIC will be measured from the start of study to discharge, and during the F/U after 12 weeks.

#### Treatment credibility and expectancy scale

2.7.3

To assess the expectation that the participants have about the treatment, a 9-point Likert scale is used for assessment. Prior to the first treatment, the participants will be asked “how much do you expect this treatment to alleviate your symptoms?” The response to this question will be scored (1 = not at all; 5 = somewhat; and 9 = very much).

#### Medication use

2.7.4

The type, dose, and frequency of medication used by the participants during the study period will be investigated during the visits.

#### Adverse events

2.7.5

An adverse event (AE) refers to any undesirable and unintended sign, symptom, or disorder that appears during the clinical trial. AEs will be checked during each visit and recorded without exception. AEs do not necessarily need to show a causality with the treatment applied in this study. The researcher will analyze the frequency of AEs and serious AEs (SAEs) suspected to be associated with the treatment. Collected safety data will be adequately summarized and all SAEs will be described in detail. An SAE^[31]^ is an AE that:

1.causes death or is life-threatening;2.requires hospitalization or prolongs hospitalization;3.causes persistent or significant disability or dysfunction; or4.an otherwise medically important situation.

The researcher will assess the causality between AEs that occur and each treatment method by a 6-step scale in accordance with the WHO-UMC causality assessment system^[32]^: 1 = definitely related; 2 = probably related; 3 = possibly related; 4 = probably not related; 5 = definitely not related; and 6 = unknown. The severity of AEs will be classified into 3 levels according to the Spilker classification^[33]^:

1.mild = an AE that does not significantly impair daily activities (function) nor require additional medical intervention;2.moderate = an AE that significantly impairs the normal life (function) of the participant, and may require additional medical intervention but resolves afterwards; and3.severe = an SAE that requires intense medical intervention, and results in sequelae.

Actions for procedure after an AE will be classified and recorded as follows:

1.not applicable (no effect on the procedure);2.temporary discontinuation; and3.permanent discontinuation.

The F/U outcome of the AE will be classified and recorded as follows:

1.recovered, no sequelae;2.recovered with sequelae;3.recovering, persistent AE, no progress;4.no recovery, presence of AE, progressing;5.death; and6.unknown.

Actions taken other than planned treatment following an AE will be classified and recorded as follows:

1.none;2.drug therapy;3.hospitalization/prolonged hospitalization;4.therapeutic or diagnostic procedure; and5.others.

To prevent random group allocation being revealed during AE assessment, AE assessments will be reported in a separate case report by a designated investigator. The severity and causality of AEs and actions taken will be assessed according to the procedure described above. In this study, safety of the treatment will be assessed by identifying the frequency and severity of AEs and comparing them between the 2 groups.

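### The AE severity grades mix intensity with seriousness and outcome, so intense events that resolve are graded moderate and impairing events still ongoing have no grade

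*Protocol article*

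**What the plan says.** Section 2.7.5 (Adverse events) states: "The severity of AEs will be classified into 3 levels according to the Spilker classification". The three levels are:

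- "mild = an AE that does not significantly impair daily activities (function) nor require additional medical intervention"
- "moderate = an AE that significantly impairs the normal life (function) of the participant, and may require additional medical intervention but resolves afterwards"
- "severe = an SAE that requires intense medical intervention, and results in sequelae"

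The abbreviation SAE means serious, not severe, as the same section shows: "The researcher will analyze the frequency of AEs and serious AEs (SAEs) suspected to be associated with the treatment". Seriousness has four criteria of its own. One of them, "requires hospitalization or prolongs hospitalization", does not depend on lasting harm.

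The section also codes the follow-up outcome of each AE on a separate six-category list. That list distinguishes recovery with sequelae from recovery without, and codes 3 and 4 are for events that persist. Further lists record the effect on the study procedure and any other action taken.

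At the end of section 2.7.5, safety is to be assessed by "identifying the frequency and severity of AEs and comparing them between the 2 groups".

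**The concern.** Severity describes how intense an event was. Seriousness and outcome are different attributes, and section 2.7.5 gives each its own field. The severity scale should add the intensity information that those fields lack. Instead, its top grade requires seriousness and sequelae as well as intensity, and its middle grade requires resolution.

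Two things follow. The severe category is narrower than its name suggests. Also, a significantly impairing event cannot be graded until its outcome is known, although AEs are checked at every visit.

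Safety is a stated objective (section 2.1), and the severity grade feeds the planned safety comparison directly. The experimental arm adds traction and walking with needles in place (section 2.5.1). A short, intense reaction that resolves is one kind of harm that a severity table ought to be able to show. Under these definitions it cannot appear in the top row.

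**Working it through.** The document gives no AE rate and no figure to reproduce, so this is a check of logic: do the three definitions, applied as written, cover the events that the section itself expects?

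**Inputs, all from section 2.7.5**

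| Grade | Significant impairment | Intervention | SAE required | Outcome required |
|---|---|---|---|---|
| Mild | no | none additional | no | none stated |
| Moderate | yes | optional | no | resolves |
| Severe | not stated | intense | yes | sequelae |

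**Step 1. List the combinations.** Take impairment (no, yes), intervention (none, additional, intense), SAE (no, yes) and outcome (resolved without sequelae, sequelae, ongoing, death). Death is possible only for an SAE, so there are 4 outcomes for an SAE and 3 for a non-serious event. The total is 2 × 3 × (4 + 3) = 42.

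**Step 2. Apply the definitions**, reading resolution as resolution without sequelae and not counting death as sequelae.

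- Mild: no impairment, no intervention: 1 × 1 × 7 = 7.
- Moderate: impairment, resolved: 3 interventions × 2 SAE states = 6.
- Severe: SAE, intense intervention, sequelae: 2 impairment states = 2.
- No grade: 42 − 7 − 6 − 2 = 27.

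These are counts of definitional combinations, not of expected events. They show that the scale is not exhaustive and say nothing about how often a gap will be met.

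**Step 3. Look at the cases that matter.**

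- *Impairing, intense intervention, resolved without sequelae:* moderate, whether or not it is an SAE. An impairing event that needed no treatment and resolved gets the same grade.
- *Impairing and still ongoing:* 3 interventions × 2 SAE states = 6 combinations, none of them graded. Moderate fails because the event has not resolved, and severe fails because sequelae have not been established. Outcome codes 3 and 4 show that such events are expected.

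**Step 4. Vary the reading.**

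- If resolution includes recovery with sequelae, the 6 impairing combinations with sequelae also become moderate. One of them is already severe, so 5 leave the ungraded set (27 − 5 = 22), and one combination now fits two grades.
- If intense intervention is taken to exceed what moderate allows, with its phrase "may require additional medical intervention but resolves afterwards", then the resolved intense event is ungraded rather than moderate.

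Under neither variation does the resolved intense event become severe or the ongoing impairing event gain a grade.

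**The case against.** The strongest reply is that little information is lost. Every AE is to be recorded, every SAE gets a detailed account, and separate codes cover outcome, interruption of the procedure and other action taken. An intense reaction that resolves would appear in the AE frequency, in the action and outcome codes and, if serious, in a narrative. This stands. A reader might infer that the rule hides such events from the safety report, and the document does not support that. What is affected is the event's place in the severity comparison.

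A reader might also infer that a large class of intense but non-serious events is barred from the severe grade. On the wording they are barred, but the class is probably small. The fourth SAE criterion is an open category for medically important events, and prolonged hospitalization also qualifies in a trial that treats inpatients.

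The wording is attributed to a published classification that cannot be checked here, and section 2.10.1 promises an operating procedure and training on completing case reports. Both could limit misgrading in practice. Neither changes the printed definitions, which form a complete three-level rule rather than a detail left for another document. No other section supplies a different rule.

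Finally, the document sets no decision threshold on severe counts, and the primary outcome, NRS for low back pain at day 4, is untouched. This is fair, and it bears on priority.

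**Conclusion.** The point holds as a defect in how the severity scale is defined. As written, an impairing event that needs intense intervention and resolves is graded moderate, and a significantly impairing event that is still ongoing has no grade. The between-group severity comparison therefore under-counts severe events in either arm and is less able to show a difference in intense reactions.

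The size of the under-count cannot be computed, because the document gives no expected AE frequency or severity. To say that all resolved intense events are excluded from the severe grade only restates the definition and is not a magnitude.

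A reader might also infer that the rule favours one arm. The document does not support that: the same definitions apply to both groups. What is shown is a loss of sensitivity.

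The conclusion rests on reading the definitions literally and on SAE meaning a serious event, as the section spells out. Low priority, because the separate SAE, outcome and action records largely compensate.

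**What to change.** Reword the three severity levels in section 2.7.5 so that they depend on intensity or functional impact alone and so that every AE falls into exactly one level when it is assessed. Remove the SAE and sequelae conditions from severe and the resolution condition from moderate. Leave seriousness to the four SAE criteria and sequelae or recovery to the six-category outcome list, both of which already exist. Then compare AEs by severity between arms on the reworded scale.

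The change needs an edit to the definitions and matching guidance for the case report form, with no new data items. The downside is a small departure from the wording attributed to the cited three-level classification, which should be stated when results are reported.
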